### Study design

2.1

This is a multicenter, central-randomized, single-blind, sham-controlled, noninferiority clinical trial. In all, 208 participants will be randomized into 2 groups at a ratio of 1:1. Participants in the treatment group will be treated with traditional acupuncture and placebo medicine. Participants in the control group will be treated with sham-acupoint acupuncture and medicine (fluoxetine hydrochloride tablets).

The whole study period is 25 weeks, including 1-week baseline observation, 12-week treatment, and 12-week follow-up. Patients will be evaluated with scales for clinical efficacy before and the 2nd, 4th, 8th, 12th week of treatment, and 24th week of follow-up, and monitored by proton magnetic resonance spectroscopy (^1^H-MRS) and serum for acupuncture mechanisms before and the 12th week of treatment (Fig. 1).

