### Estimation of sample size

2.11

Based on the previous pilot study,^[25]^ the mean change in HAMD-17 before and after treatment was used as the indicator for the efficacy evaluation in the calculation of the sample size. Results from our previous studies showed that the mean HAMD-17 scores change was 10.49 ± 4.55 after acupuncture treatment and 10.24 ± 4.46 after fluoxetine treatment. Thus, we performed a noninferiority test to calculate the appropriate trial sample size with 90% power, beta of 0.1, alpha of 0.05. The results showed that a clinically important difference can be detected by a sample size of at least 84 in each group. This number was then increased to 104 per group to allow a predicted 20% dropout rate. We will plan to enroll in all 208 participants in this study.

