### Statistical analysis

2.13

Data analysis will be based on intention-to-treat analysis (ITT) and/or per-protocol analysis (PP) principle in the light of missing data. We will also evaluate the group effect by comparing the analysis results between the above 2 data sets to evaluate robustness of our analytical results.

All data will be analyzed using SPSS19.0 (v19.0, SPSS Inc., Chicago, IL) in the China Academy of Chinese Medical Sciences (CACMS). A *P* value <.05 will be considered as significant. Descriptive statistics will be performed with mean, standard deviation (SD), maximum, minimum, and so on by groups and time.

Baseline characteristics of patients will be summarized by groups and compared with chi-square for categorical variables, and 2-sample *t* tests (normal distributions) or Wilcoxon rank-sum test (non-normal distributions) for the continuous variables. Primary and secondary outcomes according to the measurement times are applicable to univariate repetitive measurement deviation analysis or 2-sample *t* tests, or Wilcoxon rank-sum test. If there is a violation of distribution assumption, appropriate transformation will be used.

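### The transformation rule in section 2.13, and its open rank-sum option, could take HAMD-17 off the point scale on which the noninferiority trial is sized

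*Protocol article*

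**What the plan says.** Section 2.1 of the protocol article describes a "single-blind, sham-controlled, noninferiority clinical trial". Section 2.11 states that "the mean change in HAMD-17 before and after treatment was used as the indicator for the efficacy evaluation". Its pilot values are that "the mean HAMD-17 scores change was 10.49 ± 4.55 after acupuncture treatment and 10.24 ± 4.46 after fluoxetine treatment". The calculation was done "with 90% power, beta of 0.1, alpha of 0.05" and gives 84 per group, raised to 104 for dropout.

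Section 2.13 states: "Primary and secondary outcomes according to the measurement times are applicable to univariate repetitive measurement deviation analysis". The same sentence offers two-sample t tests or the Wilcoxon rank-sum test as alternatives. The next sentence is "If there is a violation of distribution assumption, appropriate transformation will be used". No test or threshold for a violation, no particular transformation and no back-transformation is given. The section also promises summary statistics, including means and SDs, for each group and time point.

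Section 2.13.1 is more specific. HAMD-17 and SDS go to the repeated-measures analysis. The t test and the rank-sum test are named only for the spectroscopy and serum markers. A significant group effect on HAMD-17 is read as showing a difference between groups.

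**The concern.** A noninferiority conclusion needs one quantity: a between-group difference whose confidence limit can be compared with a margin on the same scale. Section 2.11 sizes the trial on mean change in HAMD-17, so that scale is HAMD points. The transformation rule in section 2.13 covers primary outcomes without exception and depends on what the data look like. If it is followed for HAMD-17, the planned inference moves to a log, square-root or other scale. If the general list is read as covering HAMD-17, it may end in a rank P value. Neither can be compared with a margin in points. At stake is whether the main efficacy result could still answer the question the trial was sized for.

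**Working it through.** **1. The scale the design needs.** Inputs from section 2.11: SDs 4.55 and 4.46, changes 10.49 and 10.24, power 90%, alpha 0.05 (sidedness not stated), n = 84 per group. The article gives no numerical margin, so 84 cannot be reproduced directly. Solving backwards:

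- Pooled SD = √[(4.55² + 4.46²)/2] = √20.297 = 4.505.
- Pilot difference δ = 10.49 − 10.24 = 0.25 in favour of acupuncture.
- Margin M = SD × (z for 1−α + z for 0.90) × √(2/84) − δ, with 4.505 × √(2/84) = 0.695.
- One-sided 0.025: 0.695 × (1.960 + 1.282) = 2.25 with δ = 0; 2.00 with δ = 0.25.
- One-sided 0.05: 0.695 × (1.645 + 1.282) = 2.03 with δ = 0; 1.78 with δ = 0.25.
- Forward check, M = 2, one-sided 0.025, δ = 0.25: n = 2 × 20.297 × 3.242² / 2.25² = 84.3, which is 85 rounded up, against 84 stated.
- Dropout: 84/0.8 = 105, against 104 stated.

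So the sample size corresponds to a margin of about 1.8 to 2.25 HAMD points.

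**2. What a switch would return.** A log-scale contrast is a ratio, and a ratio does not map to a fixed number of points. In the simulations of step 3, the average week-12 score was 4.99 with an assumed baseline mean of 15 and 9.23 with one of 20. Two points on 4.99 is a ratio of 6.99/4.99 = 1.40; on 9.23 it is 11.23/9.23 = 1.22. A rank-sum P value carries no estimate in points at all.

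**3. Would the rule fire?** The article gives no baseline mean and no normality test. The figures below therefore rest on assumptions: Shapiro-Wilk at 0.05, integer scores, baseline limited to the 7 to 24 of the inclusion criteria, a floor at 0, and the pilot changes.

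Change correlated 0.5 with baseline, 84 to 104 per group, rejection in at least one arm:

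| Assumed baseline mean/SD | Raw week-12 score | Change |
|---|---|---|
| 15/4 | 100% | 19–24% |
| 18/4 | 59–76% | 20–24% |
| 20/3 | 21–26% | 19% |

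Change independent of baseline, 84 per group, rejection per arm: 99–100% for raw week-12 scores with a uniform baseline or one of 17/4, about 23% with 20/3, and 11–22% for change. Counted per trial, a per-arm rate of 20% becomes 1 − 0.80² = 36%.

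Much of the rate for change is not skewness. Normal changes merely rounded to whole points were rejected in at least one arm in 19.6% of runs, against 1 − 0.95² = 9.75% for two exact tests.

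**4. Is the switch needed?** With 84 per arm and floored week-12 scores, the 95% t interval for the raw mean difference covered 94.6% (baseline mean 15) and 95.0% (18). The type I error of the plain t test was 4.9%. The raw scale is usable even where a normality test rejects.

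**The case against.** The strongest reply is that section 2.13 is only an overview. Section 2.13.1 then assigns the methods, and HAMD-17 gets repeated-measures analysis. This largely stands for the rank-sum test: that route to HAMD-17 rests only on the general sentence, and the explicit normal/non-normal choice in 2.13 concerns baseline characteristics. It does not dispose of the transformation rule, which 2.13.1 leaves untouched.

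A second reply is that the normality criterion and the choice of transformation belong in a statistical analysis plan, which is not shown. That is fair, and their absence is not the point. The point is a rule that is stated, reaches the primary outcome and does not suit the design.

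Four stronger readings are tempting but not supported:

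- A reader might infer that the rule is bound to fire. The simulated rate depends on the variable tested and on a baseline mean the article does not give. Checking every arm at all six time points produced at least one rejection in 98–100% of trials. However, twelve independent tests of exactly normal data would do so in 1 − 0.95¹² = 46%, and at a threshold of 0.05/12 the range was 21–100%.
- A reader might infer that the options inflate the type I error. Taking the best of t, Wilcoxon and log-t gave 6.4–6.8%, but the plan does not permit that. A normality-driven switch gave 5.0–5.1%.
- A reader might infer that no estimate in points would survive. Group means and SDs at each time point would; the planned inferential estimate would not.
- A reader might infer that the switch displaces a noninferiority analysis. Section 2.13.1 describes only a test of difference and section 2.11 gives no margin, so none is stated there to displace.

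**Conclusion.** The concern holds in limited form. As written, section 2.13 allows a data-driven, unspecified transformation of a noninferiority outcome sized in HAMD points, and its general list is not reconciled with section 2.13.1 on the rank-sum test. Following either route would leave no formal between-group estimate with a confidence limit to compare with a margin of about 1.8 to 2.25 points (itself back-calculated under assumptions on sidedness and true difference).

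The chance of this happening cannot be fixed from the article: about 11–24% for change and about 20–100% for raw week-12 scores, mixing per-arm and either-arm counts, under assumed baselines and an assumed Shapiro-Wilk test. The harm is to interpretability, not to type I error. Because raw-scale inference performs well in the settings simulated, the switch buys nothing. It should be changed, but removing it alone would not supply a noninferiority analysis; the raw-scale estimate must also be tied to a margin.

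**What to change.** In sections 2.13 and 2.13.1, state that:

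- the primary HAMD-17 analysis stays on the original scale whatever the distribution, as a model-based between-group mean difference in change with a 95% confidence interval;
- noninferiority is judged by comparing the relevant limit of that interval with the margin, given as a number in HAMD points;
- transformed, rank-based or bootstrap analyses of HAMD-17 are sensitivity analyses only;
- the choice between t test and rank-sum test applies to the spectroscopy and serum markers, as 2.13.1 already has it.

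The cost is a few sentences of analysis wording, settled before unblinded data are seen. No visit, measurement or patient is added. The margin should be the one used for the sample size, so 84 per group need not change on this account.

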#### Primary outcomes

2.13.1

We will use univariate repetitive measurement deviation analysis with HAMD-17 and SDS scores before and the 2nd, 4th, 8th, 12th week of treatment, and 24th week of follow-up as the outcomes. A significant effect of group indicates that the HAMD-17 and SDS scores are different between groups after interventions.

The diversity of Cho, NAA, MI, Glx, Cr, Cho/Cr, Cho/NAA, and Cr/NAA will be compared with 2-sample *t* tests or Wilcoxon rank-sum test with their concentrations or ratios before and the 12th week of treatment as the outcome variables. Similar analysis approach will be used for the levels of 5-HT, NE, DA, BDNF, IL-4, IL-6, IL-10, IL-18, IL-1β, and TNF-α in serum.

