## Introduction

1

Poststroke depression (PSD) is a serious and common complication of stroke.^[1]^ Reports revealed that the prevalence of PSD was from 30% to 65%.^[2,3]^ PSD has been associated negatively with survival, cost of medical care, and compliance with therapy including rehabilitation, functional outcome, resumption of social activities, and quality of life.^[4]^

At present, the treatment of PSD mostly applies selective serotonin reuptake inhibitors (SSRIs). A meta-analysis of randomized controlled trials for PSD has revealed that patients in the SSRIs group had make great improvement in depressive symptoms significantly compared with the placebo group.^[5]^ Several controlled studies have demonstrated that while some patients made improvement on depression scores significantly, others discontinued due to side effects.^[6,7]^ And SSRIs have slow onset speed about 3 to 4weeks.^[5]^ A trial suggested that the advantages of fluoxetine hydrochloride could not be demonstrated within the first 3 months compared with controlled treatment.^[8]^ On the contrary, the use of antidepressants might also increase the risk of interactions derived from various drugs, as most stroke patients concurrently take.^[9]^

Acupuncture is 1 of the main treatments of traditional Chinese medicine (TCM) which has been used for over 2000 years. Acupuncture is widely used in the treatment of PSD. A meta-analysis has demonstrated that the curative effect of acupuncture on PSD was superior to antidepressants among waitlist controls in improving both response and symptom severity.^[10]^ Another meta-analysis revealed that there is no difference in effective rate on comparison between the acupuncture group and western medicine group in treating PSD.^[11]^

In China, because of the good effect, more and more patients are willing to choose acupuncture for PSD. However, no sufficient clinical trial data and solid evidence could confirm whether acupuncture could yield certain efficiency in treating PSD and how acupuncture works. It is necessary to verify the effectiveness and mechanism of acupuncture from senior quality studies. Now, the evidence about acupuncture effect on treating PSD is inadequate and must apply further strictly design clinical studies.

The primary objectives of this study are to evaluate the efficacy and mechanism of acupuncture treatment and follow-up on PSD during 6 months.

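### The primary HAMD-17 test is a group effect averaged over six visits including baseline, so it is neither a post-treatment difference nor the before-to-after change the trial was sized on, and in a noninferiority trial the dilution favours the claim.

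*Protocol article*

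**What the plan says.** - **Design.** Section 2.1: "This is a multicenter, central-randomized, single-blind, sham-controlled, noninferiority clinical trial". Treatment lasts 12 weeks and a 12-week follow-up comes after it, so week 24 is off treatment.
- **Sample size.** Section 2.11: "the mean change in HAMD-17 before and after treatment was used as the indicator for the efficacy evaluation". The inputs are "the mean HAMD-17 scores change was 10.49 ± 4.55 after acupuncture treatment and 10.24 ± 4.46 after fluoxetine treatment", "with 90% power, beta of 0.1, alpha of 0.05". The result is 84 per arm, and "This number was then increased to 104 per group to allow a predicted 20% dropout rate".
- **Primary analysis.** Section 2.13.1: "We will use univariate repetitive measurement deviation analysis with HAMD-17 and SDS scores before and the 2nd, 4th, 8th, 12th week of treatment", with the week-24 score added as a sixth outcome. It reads a significant group effect as showing that the arms' scores differ once treatment has been given.
- **Other tests.** Section 2.13 also allows two-sample t tests or Wilcoxon tests in general terms, but 2.13.1 names only the repeated-measures ANOVA for HAMD-17 and SDS. Section 2.13.2 uses the same six-visit approach for NIHSS, MBI, the TCM stroke criteria and CGI.
- **Missing data.** Section 2.13 refers to ITT and/or per-protocol sets depending on missing data and compares the two. It states no imputation rule and no complete-case rule.

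**The concern.** The between-subject group term in this ANOVA compares each patient's mean over all visits. With baseline among the outcomes, one sixth of the weight falls on a visit at which the arms cannot differ in expectation. A further sixth falls on a visit 12 weeks after treatment ends. A third falls on weeks 2 and 4, and the Introduction says of the comparator's class: "And SSRIs have slow onset speed about 3 to 4weeks". The document therefore gives the group term a meaning it does not have, and tests something other than what it was sized for.

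The direction of the error matters. In a superiority trial, dilution toward no difference works against the sponsor's hypothesis. Here the hypothesis is noninferiority, so dilution makes a truly worse acupuncture arm look closer to fluoxetine.

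**Working it through.** **1. The plan's own figure.** Pooled SD of change = √((4.55² + 4.46²)/2) = 4.505. Section 2.11 says "we performed a noninferiority test to calculate the appropriate trial sample size" but prints neither a margin nor the sidedness of alpha, so 84 cannot be reproduced directly. Solving margin = SD × √(2/84) × (z₁₋α + z₀.₉₀) − true advantage, with SD × √(2/84) = 0.695, gives:

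- one-sided 0.025: 2.25 (true difference 0) or 2.00 (acupuncture 0.25 better, from 10.49 − 10.24);
- one-sided 0.05: 2.03 or 1.78.

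A margin of 2 is used below as an assumption; the implied range is 1.78 to 2.25. Dropout: 84/0.8 = 105, against 104 stated, a trivial difference.

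**2. Dilution of the estimate.** The six-visit difference always equals 5/6 of the mean difference over the five post-baseline visits, because baseline contributes zero in expectation. How that relates to week 12 depends on the profile, which the documents do not give. Assumed profiles at baseline and weeks 2, 4, 8, 12, 24, with week 12 set to 1:

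| Profile | Weights | Share of week-12 difference | A 2.0-point difference becomes |
|---|---|---|---|
| Immediate, lasting | 0, 1, 1, 1, 1, 1 | 5/6 = 0.83 | 1.67 |
| Linear onset, lasting | 0, 1/6, 1/3, 2/3, 1, 1 | 0.53 | 1.06 |
| Linear onset, gone by week 24 | 0, 1/6, 1/3, 2/3, 1, 0 | 0.36 | 0.72 |

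**3. Standard error of the six-visit average.** Assume equal correlation ρ between visits. The per-visit SD is s = 4.505/√(2(1 − ρ)) and the SD of a patient's six-visit mean is s√((1 + 5ρ)/6). At ρ = 0.5, s = 4.505, the SD of the mean is 3.44, and the SE of the arm difference at 84 per arm is 3.44 × √(2/84) = 0.531.

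**4. False noninferiority.** The true week-12 deficit equals the assumed margin of 2, and the margin is applied to the six-visit average by a 95% interval. The probability of declaring noninferiority is Φ((2 − diluted deficit)/SE − 1.96). At ρ = 0.5:

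- immediate, lasting: Φ(0.333/0.531 − 1.96) = 9%;
- linear, lasting: Φ(0.944/0.531 − 1.96) = 43%;
- linear, gone: Φ(1.278/0.531 − 1.96) = 67%.

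The nominal rate is 2.5%. As ρ goes from 0.3 to 0.7, the three figures run from 14% to 6%, 70% to 23%, and 92% to 38%.

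**5. Power to detect a true 2-point week-12 deficit (two-sided 0.05, 84 per arm).**

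- Week-12 change: Φ(2/0.695 − 1.96) = 82%.
- Week 12 adjusted for baseline, ρ = 0.5: SD = 4.505 × √(1 − 0.25) = 3.90, SE = 0.602, power 91%.
- Group effect, immediate and lasting: 99%, 88%, 57% at ρ = 0.3, 0.5, 0.7.
- Group effect, linear and lasting: 79%, 51%, 27%.
- Group effect, linear and gone: 48%, 27.5%, 15%.

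Power of the group effect thus falls on both sides of the 82% for change.

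**The case against.** **Week 24 fits a stated aim.** The Introduction sets the objective over six months, treatment and follow-up together. This stands as a reason to measure and report week 24. It is no reason to fold it into the average, and it does not touch baseline. Week 24 dilutes only if the difference fades; a lasting or growing difference would not be shrunk by it.

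**Averaging can gain power.** True. With immediate, lasting onset the group effect beats week-12 change (88% against 82% at ρ = 0.5). A reader might infer that power is always lost; the calculation does not support that. The mismatch with the sized quantity and the dilution by baseline remain under every profile.

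**Early visits.** A reader might infer that no difference can exist at weeks 2 and 4 because SSRIs act slowly. The documents do not support this: only baseline has a zero expected difference. If acupuncture acts sooner, those visits could favour it, which would also move the average away from the week-12 comparison.

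**Missing visits.** A reader might infer that the plan drops every patient with a missing visit. It does not say so. Section 2.13 names ITT, and an imputation rule may sit in an analysis plan not shown. If nothing is imputed, classical repeated-measures ANOVA would exclude such patients, up to about 42 of 208 (20% of 208 = 41.6) at the predicted dropout. The inflation already allows for the number (104 × 0.8 = 83 per arm), so the risk is bias more than sample size.

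**Sphericity.** This is no ground for criticism here. It concerns the within-subject tests; the between-subject group effect does not need it.

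**Conclusion.** The point holds as wrong in the text and should be corrected before analysis. Section 2.13.1 makes baseline an outcome and reads the resulting group effect as a post-treatment difference, while section 2.11 sizes the trial on change from before to after treatment. This needs no assumption beyond randomisation, and neither does the factor of 5/6 on the post-baseline average.

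The larger figures are conditional. Retention of 53% or 36% rests on an assumed linear onset. The 9%, 43% and 67% false noninferiority rates rest on an assumed margin of 2, equal visit correlation of 0.5, 84 per arm, and the margin being applied to the six-visit average. They show the direction and possible size of the error and do not predict this trial's error rate. Loss of power and exclusion of incomplete patients are possibilities, not consequences that follow from the document.

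**What to change.** - Make the primary HAMD-17 estimate the week-12 arm difference adjusted for baseline HAMD-17. One suitable model is a mixed model with post-baseline visits as outcomes, baseline as covariate and a group-by-visit term, which keeps partially observed patients. An analysis of covariance at week 12 would also cure the mismatch, but would need its own rule for missing week-12 scores.
- Judge the confidence interval of that difference against the noninferiority margin used for the sample size, and state the margin beside it. A difference test at P < .05 on the right contrast would still not test noninferiority.
- Report week 24 as a separate follow-up contrast.
- Take baseline out of the outcomes for SDS and the secondary scales as well.

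The cost is analysis wording only. Visits, scales and sample size stay as they are.

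### The trial is declared and sized as noninferiority, but the only primary analysis printed is a P<.05 test for a difference, whose expected non-significant result cannot show noninferiority

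*Protocol article*

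**What the plan says.** Section 2.1 of the protocol article sets the framework: "This is a multicenter, central-randomized, single-blind, sham-controlled, noninferiority clinical trial".

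Section 2.11 sizes the trial in that framework, on HAMD-17 change before to after treatment: "we performed a noninferiority test to calculate the appropriate trial sample size with 90% power, beta of 0.1, alpha of 0.05". The planning values come from a pilot: "the mean HAMD-17 scores change was 10.49 ± 4.55 after acupuncture treatment and 10.24 ± 4.46 after fluoxetine treatment". The result is worded in the language of a difference: "The results showed that a clinically important difference can be detected by a sample size of at least 84 in each group". The size of that difference is not given. The figure is then raised for losses: "This number was then increased to 104 per group to allow a predicted 20% dropout rate".

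The analysis sections take another line. Section 2.13 says that a P "value <.05 will be considered as significant" and names a repeated-measures analysis, two-sample t tests or Wilcoxon tests. Section 2.13.1 assigns HAMD-17 and SDS to the repeated-measures analysis at baseline, weeks 2, 4, 8 and 12, and week 24, and says how to read it: "A significant effect of group indicates that the HAMD-17 and SDS scores are different between groups after interventions".

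Neither section mentions a noninferiority hypothesis, a margin or a confidence limit.

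**The concern.** A noninferiority claim needs a limit on how much worse acupuncture could be than fluoxetine, and data that exclude a deficit of that size. A test of no difference does neither. If significant, it says that the groups differ. If not significant, it says that a difference was not shown, which can happen when acupuncture is as good, when it is somewhat worse, or when the data are noisy.

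The pilot leads the sponsor to expect almost no difference, so a non-significant group effect is the likely outcome. The article gives no way to turn that outcome into an answer to the trial's question. The 90% power in section 2.11 was calculated for a test that does not appear in section 2.13.

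The tested quantity differs too. Section 2.11 sizes a before-to-after change. The group effect in section 2.13.1 averages over six time points, one of them before treatment and one 12 weeks after it ends.

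**Working it through.** **Inputs (section 2.11).** SDs of change 4.55 and 4.46; pilot difference 10.49 − 10.24 = 0.25 in favour of acupuncture; power 90%; alpha 0.05, sidedness not stated; 84 per arm, raised to 104. The margin is not stated, so it is treated below as an assumption with a range. Normal approximations are used throughout.

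**1. Can 84 be reproduced?** The variance sum is 4.55² + 4.46² = 20.70 + 19.89 = 40.594. For noninferiority,

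n per arm = (z_alpha + z_power)² × 40.594 / (margin + true advantage)².

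Without a margin this cannot be evaluated, but it can be solved backwards from n = 84:

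| One-sided alpha | (z sum)² | margin + advantage | Margin if advantage 0.25 | Margin if advantage 0 |
|---|---|---|---|---|
| 0.025 | (1.960 + 1.282)² = 10.507 | √(10.507 × 40.594 / 84) = 2.25 | 2.00 | 2.25 |
| 0.05 | (1.645 + 1.282)² = 8.564 | √(8.564 × 40.594 / 84) = 2.03 | 1.78 | 2.03 |

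Forward check: a margin of 2.0 with advantage 0.25 at one-sided 0.025 gives 10.507 × 40.594 / 2.25² = 84.25. So 84 is compatible with a noninferiority test at a margin of roughly 1.8 to 2.25 points, and the article does not say which.

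**2. Is 84 a size for detecting a difference?** Not the pilot difference. A two-sided 0.05 test with 90% power at 0.25 needs 10.507 × 40.594 / 0.25² ≈ 6,825 per arm.

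**3. Power of a difference test at the pilot difference.** SE = √(40.594 / 84) = 0.695, and 0.25 / 0.695 = 0.36.
- P(significant, favouring acupuncture) = 1 − Φ(1.96 − 0.36) ≈ 5.5%.
- P(significant, favouring fluoxetine) = Φ(−1.96 − 0.36) ≈ 1.0%.
- Total ≈ 6.5%, so about 93.5% of such trials end non-significant.

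**4. What would follow if non-significance were taken as success?** This reading is hypothetical. For a true deficit d, P(non-significant) ≈ Φ(1.96 − d/SE).
- 84 per arm, d = 2.0: Φ(1.96 − 2.88) ≈ 18%.
- 104 per arm, SE = √(40.594 / 104) = 0.625, d = 2.0: Φ(1.96 − 3.20) ≈ 11%.
- 84 per arm, d = 1.78 and d = 2.25 (the ends of the margin range): about 27% and 10%.

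A rule comparing a confidence limit with the margin passes a true deficit equal to that margin 2.5% of the time at one-sided 0.025, or 5% at one-sided 0.05.

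**5. Distance from the planned test.** Steps 3 and 4 use a two-sample comparison of change scores, as in section 2.11. The group effect in section 2.13.1 averages six time points. Randomization makes the expected baseline difference zero, so a constant 2-point deficit at the five later visits would average 2 × 5/6 = 1.67. The SE of that average depends on within-patient correlations that are not given, so the planned test's own operating characteristics cannot be computed.

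**The case against.** The strongest reply is that a journal article condenses a fuller protocol. The margin, its justification and a confidence-limit rule may stand there or in an analysis plan, and the phrase "a clinically important difference can be detected by a sample size of at least 84 in each group" may be a loose name for the margin. The sentence in section 2.13.1 also says what a significant model term indicates, which is not formally a criterion for trial success. This stands in part: the unprinted margin is not a serious defect on its own. It does not remove the mismatch, because the article does not defer the primary test. It prints a test and an interpretation, and both belong to a difference trial. An analysis plan that followed them would not test what sections 2.1 and 2.11 promise.

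Two stronger readings are tempting, and neither is supported. A reader might infer that no planned result could show noninferiority. That goes too far: a significant group effect favouring acupuncture would imply it at any margin, although step 3 puts the chance at about 5.5% under the pilot values. A reader might also infer that the sponsor plans to declare success when P exceeds .05. The article nowhere says so, and the 18% and 11% figures are error rates of that supposed rule, not of anything planned.

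**Conclusion.** The analysis is wrong as written for the declared design. The trial is framed and sized for noninferiority on HAMD-17 change, and the one primary test printed is a difference test on another quantity. The expected non-significant result would support no conclusion about noninferiority, and the 90% power does not apply to the printed test.

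The mismatch rests on the text alone. Its size is illustrative: it assumes a two-sample comparison of change scores, the pilot SDs, and for the error rates a 2-point margin that the article does not state. The 2.5% comparator further assumes one-sided 0.025; section 2.11 says only alpha 0.05, and at one-sided 0.05 the comparator is 5%. This should be corrected before results are interpreted, because it concerns the main conclusion of the trial.

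**What to change.** 1. In sections 2.13 and 2.13.1, make the primary analysis the between-group difference (acupuncture minus fluoxetine) in HAMD-17 change from baseline to week 12, the quantity that was sized, with a confidence interval at the alpha used for sizing. Conclude noninferiority only if the limit unfavourable to acupuncture lies inside the margin.
2. In section 2.11, print the margin, the sidedness of alpha and the assumed true difference actually used to obtain 84. If the margin was 2.0 with the 0.25 advantage counted at one-sided 0.025, it helps to add that power at true equality is Φ(2.0/0.695 − 1.96) ≈ 82% with 84 per arm.
3. Replace the statement that a clinically important difference can be detected with noninferiority wording.
4. Keep the repeated-measures analysis as supportive, and amend its interpretation so that a non-significant group effect is not taken as evidence of noninferiority.

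The cost is wording and analysis work, with no extra patients or data. The condition is that the margin must be the one documented at sizing, not one chosen after results are seen. The trial is described as single-blind and section 2.6 places its conduct from May 2016, so a margin that cannot be traced to the original calculation would be open to challenge and should be reported as such.
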